### Rationale for the explorative study

Continuous therapy with rifaximin in combination with lactulose significantly reduces the risk of overt HE, recurrence and HE-related hospitalization in randomized double-blind placebo-controlled clinical trials [1–3]. Rifaximin is approved for the therapy of *overt* HE in Germany. Therapy with lactulose has been shown to improve cognitive functions in patients with liver cirrhosis. So far, whether monotherapy with rifaximin is as effective as combination therapy with rifaximin and lactulose in the treatment of MHE, has not been addressed in a prospective clinical trial.

Rifaximin is a minimally absorbed gut-selective antibiotic and thus impacts on the intestinal microbiome. The role of the intestinal microbiome in the pathophysiology of HE is still little understood. To our knowledge, changes in the microbiome of the upper gastrointestinal (GI) tract as result of therapy with rifaximin have not yet been addressed in clinical studies and studies addressing the persistence of changes of the intestinal microbiome are scarce [19].

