## Methods and design

RiMINI is a monocentric exploratory pilot study on 60 patients with MHE as assessed by critical flicker frequency (CFF) analysis. Additionally, visual evoked potentials’ (VEP) testing, electroencephalography (EEG) and a psychometric test (NCT-A) will be carried out. The patients will be randomized to treatment either with rifaximin alone 550 mg twice daily (bid) continuously for a period of 3 months or to continuous treatment with 550 mg rifaximin bid in combination with lactulose 30–60 ml daily (to pass 2–3 semisoft stools/day) for 3 months. An esophagogastroduodenoscopy (EGD) will be performed at baseline, at the end of antibiotic treatment, as well as 6 and 12 weeks after the end of treatment to obtain gastric and duodenal biopsies and aspirates will be taken. The samples will be analyzed for their specific bacterial taxae by applying next generation sequencing (NGS) after ribonucleic acid (RNA) isolation. Additionally, stool samples will be taken at the same time points. Prevalence of *Helicobacter pylori*, which is the predominant gastric microbe, will be assessed by histology, rapid urease test and serology at study entry. For clinical assessment, quantification of MHE and therapeutic effects, CFF, EEG, VEP and psychometric tests are assessed weekly during the first month and every 4 weeks from the beginning of the second month until the end of the post-treatment follow-up.

Changes in the gut microbiome from antibiotic therapy with rifaximin alone or rifaximin with lactulose are analyzed comparing pre- and post-antibiotic time points. The follow-up data will show whether the change in the gut microbiome is persistent or transient. We will compare the effect of antibiotic therapy with rifaximin alone with a combination therapy with lactulose on the clinical course of MHE. As planned, NGS methods (Illumina sequencing, Illumina, San Diego, CA, USA) will be used to characterize the composition and changes of both stomach and small bowel microbiomes. Bacterial ribosomal ribonucleic acid (rRNA) will be isolated from aspirates, biopsies and feces and then stored in RNAlater at −80 °C. The samples will be analyzed by NGS methods as described below with the aim of identifying the microbiome of the stomach and the small bowel, as well as of the large bowel, in patients with liver cirrhosis and MHE and its changes before and after therapy (Fig. 1).

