### Randomization procedure

The randomization will be performed with the clinical database software secuTrial that is also used for the data management in the study. The two arms will be randomized in a 1:1 ratio using the minimization method described by Pocock and Simon with a stratification for age and gender.

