### Statistical analysis

All demographic and baseline variables are presented in descriptive statistics stratified by treatment arm in the full analysis set (FAS, all randomized patients). Exploratory tests, according to the level of the respective variables, will search for differences between both arms which might occur despite randomization. The primary target variable is compared between both treatment arms. The odds ratio for treatment success is calculated between both treatment arms together with the corresponding two-sided 95 % confidence interval. If the confidence interval is completely above or below the threshold of 1, the superiority of the corresponding treatment arm with larger success rates can be concluded. If the confidence interval covers the threshold of 1, then the lower and upper confidence limits give limits which can be used in non-inferiority statements. This analysis is performed primarily in the modified full analysis set (MFAS, all randomized patients but excluding those with missing CFF tests) according to the ITT principle. Missing values are imputed by the last observation carried forward principle.

Secondary analyses for the primary target variable include (1) logistic regression analysis with treatment arm, sex, age and baseline value of CFF as co-variables, (2) analog analyses in the per protocol set (PPS, patients of the MFAS excluding those with severe protocol violations), (3) analog analyses for the result of CFF at end of follow-up, (4) description of the results of the psychometric tests (mean and standard deviation) per treatment arm and comparison in two-sample *t* tests (both at end of treatment and end of follow-up).

The secondary efficacy variables are compared between the treatment arms in analysis of covariance (ANCOVA) models with treatment arm, sex, age and respective baseline variable as factors or co-variables, respectively.

Safety analysis is done in the safety set (SS, patients receiving at least one treatment) in descriptive and exploratory analyses. Laboratory variables and rates of SAEs are compared between both treatment arms using the Mann-Whitney *U* test and Fisher’s exact test.

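### Limits offered for non-inferiority statements come primarily from the ITT-type set, and nothing requires the planned per-protocol limit to agree; low severity in an exploratory pilot

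*Protocol article*

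**What the plan says.** The Statistical analysis section of the protocol article compares the arms on the primary variable as follows: "The odds ratio for treatment success is calculated between both treatment arms together with the corresponding two-sided 95 % confidence interval". An interval entirely on one side of 1 supports superiority of the arm with the higher success rate. If the interval covers 1, its limits "give limits which can be used in non-inferiority statements". Both readings rest on the same set: "This analysis is performed primarily in the modified full analysis set". That set is all randomized patients except those with missing CFF tests, analysed under the ITT principle with last observation carried forward. The secondary analyses of the primary variable include "analog analyses in the per protocol set", which is the modified full analysis set without patients who had severe protocol violations. The section does not say what follows if the two sets give different limits.

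Three other places bear on this:
- The Rationale names as unanswered "whether monotherapy with rifaximin is as effective as combination therapy with rifaximin and lactulose in the treatment of MHE".
- The Blinding section makes the trial open label.
- The section on prior and concomitant medication allows concomitant therapy as needed and names only the need for another antibiotic as leading to exclusion.

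**The concern.** For a superiority reading, an ITT-type set is the cautious choice, because departures from assigned treatment usually shrink the difference. For a non-inferiority reading the same shrinkage works the other way. Here the arms differ only in lactulose. A rifaximin-alone patient who takes lactulose, or a combination patient who stops it, makes the arms more alike and moves the odds ratio towards 1. The limit on how much worse monotherapy might be then looks better than it would under the assigned treatments.

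The article leaves this route open. Treatment is known to patient and physician, and nothing in the article restricts lactulose in the rifaximin-alone arm. What is at stake is modest but not empty. The Power analysis section says the results will be the basis for planning a later confirmatory multicentre trial, so a diluted limit or effect could carry into that trial's margin and sample size.

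**Working it through.** **No stated figure to reproduce.** The article gives no success rates, power, margin, adherence rates or derivation of the sample size. The check therefore illustrates direction and size under stated assumptions.

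**Inputs from the article.** Sample size: "RiMINI is a monocentric exploratory pilot study on 60 patients with MHE as assessed by critical flicker frequency (CFF) analysis". Allocation: "The two arms will be randomized in a 1:1 ratio using the minimization method". Hence 30 per arm, all assumed to be in the analysis set. Interval: "corresponding two-sided 95 % confidence interval".

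**Assumptions, not in the article.** True success is 60% on rifaximin alone and 85% on the combination. A share x of the rifaximin-alone arm takes lactulose and then succeeds at 85%. A share s of the combination arm stops lactulose and then succeeds at 60%. The odds ratio is taken as alone/combination, so its lower limit is the one that matters for monotherapy.

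**Formulas.**
- Observed rate, alone: pA = (1 − x)·0.60 + x·0.85
- Observed rate, combination: pC = (1 − s)·0.85 + s·0.60
- OR = [pA/(1 − pA)] / [pC/(1 − pC)]
- SE of log OR = √{1/(30pA) + 1/(30(1 − pA)) + 1/(30pC) + 1/(30(1 − pC))}
- Expected Wald interval: OR·exp(±1.96·SE)

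**Worked case, x = 0.30 and s = 0.20.** pA = 0.42 + 0.255 = 0.675; pC = 0.68 + 0.12 = 0.80. OR = 2.077/4 = 0.52. SE = √(1/20.25 + 1/9.75 + 1/24 + 1/6) = 0.600. Interval: 0.16 to 1.68.

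| Crossover x | Stopping s | pA | pC | Difference (points) | OR | Expected 95% interval | Chance that interval covers 1 |
|---|---|---|---|---|---|---|---|
| 0 | 0 | 0.600 | 0.850 | −25 | 0.26 | 0.08–0.91 | 44% |
| 10% | 10% | 0.625 | 0.825 | −20 | 0.35 | 0.11–1.17 | 62% |
| 20% | 15% | 0.650 | 0.8125 | −16 | 0.43 | 0.13–1.40 | 74% |
| 30% | 20% | 0.675 | 0.800 | −12.5 | 0.52 | 0.16–1.68 | 83% |

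The last column is an exact binomial enumeration of the Wald interval at 30 per arm. Dilution acts twice: the trial reaches the branch in which limits are offered for non-inferiority more often, and the lower limit reported there is higher.

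**How much the limit would support.** In the last row, a lower limit of 0.16 against an 80% combination rate means odds of 0.16 × 4 = 0.64, or a success rate of 0.64/1.64 = 39%. The interval leaves open a monotherapy deficit of about 80 − 39 = 41 points, when the assumed true deficit is 25.

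**Against a hypothetical margin.** Take a combination rate of 70% and a true OR exactly at an illustrative margin of 0.33, with no crossover. The chance that the lower limit lies above the margin is 2.3% with no stopping, 6.1% with 20% stopping and 13.2% with 40% stopping. The margin is assumed; the article sets none.

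**The case against.** The strongest reply is that there is no non-inferiority verdict to bias. The article sets no margin, test or decision rule. It calls the study an exploratory pilot, and it warns that proof of a difference or of acceptable margins can be expected only if lactulose has a drastic effect. A reader might infer from the mechanism that the trial is likely to declare rifaximin alone equally effective merely because treatment was not followed. The documents do not support that. Even in the most diluted scenario above, the expected lower limit (0.16) lies below the assumed true odds ratio (0.26). The Rationale sentence on equal efficacy describes a gap in the evidence, not a hypothesis to be tested. This part of the reply stands and sets the severity.

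A second reply is that the per-protocol analysis is already planned. That also stands: it would be wrong to say that it is missing or barred from informing a non-inferiority statement. What remains is its rank. If the two sets disagree, the stated primary limit prevails by default. The ranking is fixed in the article itself.

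Third, the per-protocol set is not a clean remedy. It can be selected, especially in an open-label trial, and it is a subset, so its interval tends to be wider. The article also does not define a severe violation, so it is unclear whether lactulose taken in the rifaximin-alone arm would count as one. This argues against replacing the primary set, not against requiring both limits to be considered.

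Finally, an ITT effect is a legitimate target when two strategies are compared. For the superiority reading no change is suggested.

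**Conclusion.** The point holds in a narrow form. One ITT-type set is primary for two readings that departures from assigned treatment affect in opposite directions, and no agreement with the per-protocol set is required. The direction is clear if patients who change treatment respond as the other arm does: the primary limit becomes somewhat too favourable to monotherapy. The size is unknown. A lower limit of 0.16 instead of 0.08 is an example that rests wholly on assumed success rates of 60% and 85%, 30% crossover, 20% stopping and 30 analysed per arm. With so few patients the limit will usually be weak support in any case: even equal observed rates of 40–70% give an interval of about 0.33–0.36 to 2.8–3.0.

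Severity is low. The change is worth making because it is cheap and because the results feed the planning of a confirmatory trial.

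**What to change.** Add one sentence to the Statistical analysis section. The modified full analysis set stays primary for the superiority rule. Any non-inferiority statement, and any margin carried into the later confirmatory trial, is based on the less favourable of the limits from the modified full analysis set and the per-protocol set. Show the two intervals side by side, with lactulose use in each arm, so that the reader can judge how much dilution is plausible.

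The cost is small. Both analyses are already planned, and concomitant medication is recorded in the eCRF, so lactulose taken in the rifaximin-alone arm should be on file. The article does not say how intake of assigned lactulose is recorded in the combination arm; that should be confirmed. The downside is that the per-protocol set is smaller and may be selected, so its limit can be less favourable for reasons other than dilution. The text should say so when the two limits are reported.

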**Methods and design:**

RiMINI is a monocentric exploratory pilot study on 60 patients with MHE as assessed by critical flicker frequency (CFF). Additionally, visual evoked potentials’ (VEP) testing, electroencephalography (EEG) and psychometric testing (NCT-A) will be carried out. Patients will be randomized to treatment either with rifaximin alone (550 mg twice daily (bid) continuously for a period of 3 months) or with rifaximin (550 mg bid continuously) in combination with lactulose (30–60 ml daily) for 3 months. An esophagogastroduodenoscopy (EGD) will be performed at baseline, at the end of treatment and 6 and 12 weeks after the end of treatment to obtain gastric and duodenal biopsies and aspirates. The samples will be analyzed for their content of specific bacterial taxae by applying next generation sequencing (NGS) after rRNA isolation to identify the microbiome of the stomach and duodenum, and of the gut, in patients with liver cirrhosis and MHE before and after therapy.

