### Schedule of evaluations/Estimated timelines

This study consists of three phases: (1) the screening phase, (2) the treatment phase and (3) the follow-up phase (Table 1).

**Table 1 Tab1:** Clinical treatment plan

	Inclusion into study	Screening	Assignment to treatment group	Treatment phase	EOT	6 weeks after EOT	12 weeks after EOT = End of study
Time		Day −15 –day 0	0 (visit 0)	Days 1–90 (visits 1–3) −3d to +3d	Visit 3	Day 129– day 135 (visit 5) −3d to +3d	Day 171– day 177 (visit 6) −3d to +3d
Informed consent	x						
Demographics		X					
Medical history concomitant medication		X		x	X	x	X
Physical exam, vital signs, weight		X	x	x	X	x	X
ECG		X					
ECOG performance status and QOL assessment		X	x	x	X	x	X
Blood tests including pregnancy test		X	x	x	X	x	X
EGD with biopsies			x		X	x	X
	Inclusion into study	Screening	Assignment to treatment group	Treatment phase	EOT	6 weeks after EOT	12 weeks after EOT = End of study
Time		Day −15–day 0	0 (visit 0)	Days 1–90 (visits 1–3) −3d to +3d	Visit 3	Day 129– day 135 (visit 5) −3d to +3d	Day 171– day 177 (visit 6) −3d to +3d
*H. pylori* serology			x				
Stool samples			x	x	x	x	x
Rapid urease test			x				
Assessment of neurocognitive function (NCT-A, CFF, VEP, EEG)		X		Days 1–28 weekly, then every 4 weeks	>x	x	x

*CFF* critical flicker frequency, *ECG* electrocardiogram *ECOG* Eastern Cooperative Oncology group, *EEG* electroencephalogram, *EGD* esophagogastroduodenoscopy, *EOT* end of treatment, *NCT-A* number-connection test A, *QOL* quality of life, *VEP* visual evoked potentials

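### For CFF at end of follow-up, the carry-forward rule has no stop at end of treatment, so a patient with no post-treatment CFF can have an on-treatment value entered as the off-treatment result

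*Protocol article*

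**What the plan says.** The Statistical analysis section describes the primary comparison first: "The odds ratio for treatment success is calculated between both treatment arms together with the corresponding two-sided" 95% confidence interval. It is run in the MFAS, defined as "all randomized patients but excluding those with missing CFF tests". The paragraph closes with the section's only missing-data rule: "Missing values are imputed by the last observation carried forward principle". The rule is not restricted to a study phase or time point.

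The next paragraph lists secondary analyses of the primary target variable. The third is "3) analog analyses for the result of CFF at end of follow-up". It has no missing-data rule of its own.

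Treatment is limited in time. Rifaximin is given alone or "in combination with lactulose (30–60 ml daily) for 3 months", and Table 1 places the treatment phase on days 1–90. The last visit is "12 weeks after EOT = End of study", at "Day 171– day 177 (visit 6) −3d to +3d".

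CFF is also measured off treatment before that visit. Methods and design has it "every 4 weeks from the beginning of the second month until the end of the post-treatment follow-up". Table 1 marks the neurocognitive tests, including CFF, at EOT and at 6 and 12 weeks after EOT.

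**The concern.** The end-of-follow-up endpoint is CFF about 12 weeks after both study treatments have stopped. A CFF from day 90 or earlier was taken in the planned treatment phase and measures something else. An LOCF rule with no stop at EOT lets the second stand in for the first when a patient has no CFF in between. This differs from the usual objection to LOCF at end of treatment, because there the carried value at least comes from the same planned phase.

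What is at stake is the only between-arm comparison of CFF after treatment that the article names. The Power analysis section says that the results will serve to plan a later confirmatory trial, so distorted off-treatment success rates could enter that planning.

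**Working it through.** There is no plan figure to reproduce. The article gives 60 patients randomised 1:1 (about 30 per arm), but no success rates, loss rates or margin.

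**Step 1: timing (Table 1).** EOT is day 90. The 6-week visit, day 129–135, is 129 − 90 = 39 to 135 − 90 = 45 days off treatment. The last visit, day 171–177, is 81 to 87 days off treatment.

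**Step 2: what LOCF enters as the last-visit result, by time of loss.**

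- Last CFF during treatment: an on-treatment value.
- Last CFF at EOT, with none afterwards: an on-treatment value.
- Last CFF at any follow-up test (first at about 4 weeks after EOT in the text, 6 weeks in Table 1): an off-treatment value, though an earlier one.

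Only the first two groups have a value carried across the end of treatment.

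**Step 3: illustration on assumed rates.** For one arm, let e be success at the last on-treatment CFF (taken as the EOT rate), f the true success at end of follow-up, and d the share with no post-treatment CFF. Loss is assumed unrelated to outcome.

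Derived success = (1 − d)·f + d·e, so the bias is d·(e − f).

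Assume e = 70% vs 50% (EOT odds ratio (0.70/0.30)/(0.50/0.50) = 2.33) and f = 30% in both arms (true odds ratio 1.00):

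| d | Arm with e = 70% | Arm with e = 50% | Odds ratio |
|---|---|---|---|
| 10% | 0.9·0.30 + 0.1·0.70 = 34% | 0.9·0.30 + 0.1·0.50 = 32% | 1.09 |
| 20% | 0.8·0.30 + 0.2·0.70 = 38% | 0.8·0.30 + 0.2·0.50 = 34% | 1.19 |
| 30% | 0.7·0.30 + 0.3·0.70 = 42% | 0.7·0.30 + 0.3·0.50 = 36% | 1.29 |

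For d = 20%: (0.38/0.62)/(0.34/0.66) = 1.19.

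**Step 4: where the result changes.**

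- Effect fully persists (f = e): the bias is d·0 = 0 at every d.
- Success falls by the same amount in both arms, from 70% vs 50% to 50% vs 30% (odds ratio 2.33 at both times), with d = 20%: derived success is 54% vs 34%, odds ratio 2.28. Both rates are 4 points too high, but the odds ratio hardly moves.
- Rates as in Step 3, but every patient without the final CFF has an interim off-treatment CFF, with success assumed midway between e and f (50% vs 40%): the odds ratio is 1.05/1.09/1.14 at 10/20/30%. This is ordinary carry-forward within follow-up, not carry-over across EOT.

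**Step 5: size against precision.** With 30 per arm, 38% vs 34% is 11.4 vs 10.2 expected successes. SE(log OR) = √(1/11.4 + 1/18.6 + 1/10.2 + 1/19.8) = 0.54. The 95% interval around 1.19 is therefore about 0.4 to 3.4, and the shift ln 1.19 = 0.17 is about one third of a standard error.

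**The case against.** The strongest objection is the analysis set. If the follow-up analysis takes over LOCF by analogy, it takes over the MFAS as well. If the exclusion there refers to the CFF at the time point analysed, patients without a final CFF drop out and nothing is carried. The article does not say which tests are meant. But on that reading the LOCF sentence that follows would have nothing to impute for the endpoint. For the rule to have a role, some patients lacking the analysed value must remain. The ambiguity stands, and it is a reason to define the term.

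Second, that LOCF applies to this secondary analysis is inferred from the word for analogy, and the detail may sit in a document that is not shown. The inference stands as the natural reading and no more. But the article does name a rule, with no limit, and gives no other.

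Third, a reader might infer that every patient lost in follow-up is scored as if the drug effect had lasted. The documents do not support this. CFF is repeated off treatment before the last visit, so anyone lost after the first such test carries an off-treatment value. A patient who was a failure when last measured is carried as a failure.

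Fourth, upward bias requires the effect to wane, which the follow-up is meant to find out. This stands: the direction is conditional.

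Fifth, the article gives no basis for loss of 10–30% without any post-treatment CFF. For patients who reach EOT, the window before the first follow-up test is only about 4 to 6 weeks. Patients lost during treatment also count toward the share, but the rates remain assumptions, and the shift is small beside the expected interval.

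**Conclusion.** The point holds in a limited form. As written, the rule allows an on-treatment CFF to be entered as the result about 12 weeks after treatment. This concerns patients who stay in the MFAS but were lost during treatment or before the first follow-up CFF. The derived value is then not the quantity that the endpoint names.

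If the effect wanes, success rates at end of follow-up are too high. The odds ratio is pulled toward its EOT value where the two differ, and scarcely moves where they agree. If the effect persists, there is no bias. The size cannot be computed from the article; odds ratios of 1.09 to 1.29 in place of 1.00 rest wholly on the rates assumed above.

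The conclusion assumes that the follow-up analysis inherits LOCF and that the MFAS does not remove everyone without a final CFF. It concerns one secondary analysis in a declared exploratory pilot and does not touch the primary end-of-treatment comparison. It merits correction because the stated rule can supply the wrong quantity and the wording is cheap to change.

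**What to change.** In the Statistical analysis section, or in the analysis plan before the data are analysed:

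- State that for secondary analysis (3) no CFF measured at or before EOT is carried forward to end of follow-up.
- Define for each time point which missing CFF tests remove a patient from the MFAS.
- Handle patients with no post-treatment CFF by a method that does not treat on-treatment values as off-treatment results. Multiple imputation using the collected CFF visits is one example; the choice can rest with the trial statistician, given 60 patients.
- Add one sensitivity analysis that counts these patients as not having persistent success.

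The cost is a few sentences and some analysis work, with no new visits or data. The downside is a somewhat wider confidence interval for this secondary analysis than LOCF would show.

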### Primary objective

This study primarily aims at the analysis of the efficacy of MHE therapy with rifaximin alone or in combination with lactulose on the improvement of neuropsychometric and neurophysiological changes.

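### The psychometric tests are compared by unadjusted t tests although screening values exist; the plan's own ANCOVA would give more precision at almost no cost

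*Protocol article*

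**What the plan says.** The psychometric analysis is item (4) in a list of supporting analyses in the Statistical analysis section. It plans "description of the results of the psychometric tests (mean and standard deviation) per treatment arm and comparison in two-sample" t tests, with the timing "both at end of treatment and end of follow-up". No covariate is named.

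The efficacy models on either side of it are adjusted:

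- Item (1) of the list: "Secondary analyses for the primary target variable include (1) logistic regression analysis with treatment arm, sex, age and baseline value of CFF as co-variables".
- The paragraph after the list: "The secondary efficacy variables are compared between the treatment arms in analysis of covariance (ANCOVA) models". The terms it names for them are arm, sex, age and the variable's own baseline.

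Three other places bear on the choice:

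- Table 1 (Schedule of evaluations) has a row "Assessment of neurocognitive function (NCT-A, CFF, VEP, EEG") marked at screening, during treatment and in follow-up, so each patient should have a pre-treatment value. NCT-A is the only test that the Methods and design section labels psychometric.
- The Randomization procedure section specifies 1:1 minimization on age and gender.
- The Primary objective concerns the effect of therapy "on the improvement of neuropsychometric and neurophysiological changes".

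No reason is given for leaving baseline, age and sex out of item (4) alone.

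**The concern.** A score such as a number-connection time usually differs more between patients than it changes within a patient. If the screening value predicts the later value, a comparison of later values alone carries that between-patient spread in its standard error. ANCOVA on the screening value removes the predictable part.

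Age and gender were thought important enough to balance by design. The usual practice is then to include them in the model, as the section does in its other efficacy models.

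What is at stake is precision. The Power analysis section concedes that at this sample size only a drastic benefit of added lactulose is likely to be shown, and says the results will be used to plan a later confirmatory trial. The width of the confidence intervals is therefore one of the main products of this pilot.

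**Working it through.** **Inputs from the article.** 60 patients, 1:1, so n = 30 per arm. Two-sided 95% intervals are stated for the primary odds ratio; two-sided alpha of 0.05 is assumed here. No SD, effect size, power or correlation is stated, so there is no figure to reproduce.

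**Assumptions.** The baseline-to-end correlation r is taken over a range from 0 to 0.7. The standardized difference is d = 0.6, for illustration. Sex and age are given no effect on the outcome, so any gain comes from baseline alone. All 60 patients contribute.

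**Step 1: variance.** Var(t test) = σ²(2/n). Var(ANCOVA) ≈ σ²(1 - r²)(2/n). The ratio is 1 - r², and the t test would need 60/(1 - r²) patients to match.

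- r = 0.3: 1 - 0.09 = 0.91; 60/0.91 ≈ 66 patients
- r = 0.5: 1 - 0.25 = 0.75; 60/0.75 = 80 patients
- r = 0.7: 1 - 0.49 = 0.51; 60/0.51 ≈ 118 patients

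Confidence intervals shrink by √(1 - r²): to about 0.95, 0.87 and 0.71 of the t-test width.

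**Step 2: detectable difference at 80% power** (normal approximation). For the t test, 2.8016 × √(2/30) = 0.72 SD. Multiplying by √(1 - r²) gives 0.69, 0.63 and 0.52 SD for r = 0.3, 0.5 and 0.7.

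**Step 3: power at d = 0.6.** The formula columns use the noncentral t distribution with 60 - 2 = 58 degrees of freedom for the t test and 60 - 5 = 55 for ANCOVA (intercept, arm, sex, age, baseline). The simulation columns use 4,000 replicates per setting.

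| r | t test, formula | ANCOVA, formula | t test, simulated | ANCOVA, simulated |
|---|---|---|---|---|
| 0 | 62.8% | 62.7% | 63.8% | 61.8% |
| 0.3 | 62.8% | 66.8% | 62.5% | 64.4% |
| 0.5 | 62.8% | 75.1% | 61.6% | 71.8% |
| 0.7 | 62.8% | 89.2% | 63.1% | 87.9% |

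The simulated ANCOVA figures are about 1 to 3 points below the formula. The formula charges only for degrees of freedom, while the simulation also includes chance correlation between covariates and arm. Part of the gap is simulation error (standard error about √(0.63 × 0.37/4000) = 0.8 points). The simulation did not use minimization, which would reduce the imbalance in age and sex.

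**Step 4: validity.** With no true difference, the simulated rejection rate was 5.2 to 5.3% for the t test and 5.0 to 5.5% for ANCOVA. Both hold their level.

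**Step 5: fewer patients.** With 25 per arm, the formula gives 54.7% for the t test and 58.6%, 66.9% and 82.8% for ANCOVA at r = 0.3, 0.5 and 0.7. The pattern is unchanged.

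**The case against.** The strongest defence is that nothing here is wrong. Item (4) is the last of four supporting analyses, opens with description, and drives no decision. The primary analysis is an odds ratio for treatment success, with CFF as the underlying test, and item (1) already adjusts it. The size of the gain rests on a correlation that the article does not give; at r = 0.3 it is only a few points of power. All of this stands. It limits the weight of the point but does not supply a reason to leave the screening value unused.

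A reader might infer three stronger criticisms. The article supports none of them.

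- **That comparing end values does not measure improvement.** Random allocation makes the expected screening values equal in the two arms, so the expected difference in end values equals the expected difference in change. ANCOVA estimates that same quantity. Chance imbalance at baseline is already reflected in the t test's standard error.
- **That the plan has two rules for the same variables.** The article never lists its secondary efficacy variables, and its stated secondary objective is the microbiome. The text can be read as one method for each class of variable. Item (4) then departs from the section's general practice without explanation, but an overlap is not shown.
- **That this leaves room to choose a method after seeing the results.** That would need the overlap. For the psychometric tests the article fixes one method.

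Leaving out the minimization factors does not bias the comparison either. If age or sex predicts the score, the unadjusted test tends to be conservative.

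**Conclusion.** The point holds as one of efficiency. Item (4) uses a valid, unbiased test that sets aside a screening value the trial collects and the two factors it minimizes on, while the efficacy models around it use all three. The loss is a variance factor of about 1 - r²: 0.91, 0.75 and 0.51 at assumed r of 0.3, 0.5 and 0.7. At r = 0 the cost of adjusting is 0.1 point of power by formula and about 2 points in simulation, so there is little to lose.

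These sizes depend on the assumed r, on approximately normal outcomes and on all 60 patients contributing. Any predictive value of age and sex would add to the gain. Type I error and the primary analysis are unaffected. This is a worthwhile free improvement to a secondary analysis in an exploratory pilot.

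**What to change.** In item (4), replace the two-sample t tests with the ANCOVA that the section already specifies: arm, sex, age and the respective screening value, fitted at end of treatment and at end of follow-up. Report the adjusted mean difference with its 95% confidence interval at each time point. Keep the raw means and SDs per arm as description; they remain useful for planning the later trial.

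If test times are to be transformed, fix the transformation before the outcome data are examined rather than letting it depend on the residuals. If the t test is preferred for a reason that the article does not give, state that reason.

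The cost is about one sentence in the protocol or statistical analysis plan. No new data, visits or patients are needed.
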